## Abstract

**Background:**

Major depressive disorder (MDD) is one of the most common psychiatric disorders, however, current treatment options are insufficiently effective for about 35% of patients, resulting in treatment-resistant depression (TRD). Repetitive transcranial magnetic stimulation (rTMS) is a form of non-invasive neuromodulation that is effective in treating TRD. Not much is known about the comparative efficacy of rTMS and other treatments and their timing within the treatment algorithm, making it difficult for the treating physician to establish when rTMS is best offered as a treatment option. This study aims to investigate the (cost-)effectiveness of rTMS (in combination with cognitive behavioral therapy (CBT) and continued antidepressant medication), compared to the next step in the treatment algorithm. This will be done in a sample of patients with treatment resistant non-psychotic unipolar depression.

**Methods:**

In this pragmatic multicenter randomized controlled trial 132 patients with MDD are randomized to either rTMS or the next pharmacological step within the current treatment protocol (a switch to a tricyclic antidepressant or augmentation with lithium or a second-generation antipsychotic). Both groups also receive CBT. The trial consists of 8 weeks of unblinded treatment followed by follow-up of the cohort at four and 6 months. A subgroup of patients (*n* = 92) will have an extended follow-up at nine and 12 months to assess effect decay or retention. We expect that rTMS is more (cost-)effective than medication in reducing depressive symptoms in patients with TRD. We will also explore the effects of both treatments on symptoms associated with depression, e.g. anhedonia and rumination, as well as the effect of expectations regarding the treatments on its effectiveness.

**Discussion:**

The present trial aims to inform clinical decision making about whether rTMS should be considered as a treatment option in patients with TRD. The results may improve treatment outcomes in patients with TRD and may facilitate adoption of rTMS in the treatment algorithm for depression and its implementation in clinical practice.

**Trial registration:**

This trial is registered within the Netherlands Trial Register (code: NL7628, date: March 29th 2019).

## Background

Major depressive disorder (MDD) is one of the most common psychiatric disorders, with over three hundred million people affected worldwide [1]. The mortality rate is nearly twice as high in individuals with MDD, not only in clinical but even in subclinical depression, and MDD is the second leading cause of years lived with disability (YLD), with an estimated global loss of more than 63 million healthy years in 2010 [2, 3]. Next to the burden for patients and those who care for them, MDD has a substantial economic impact, with estimated yearly costs of €91 billion and $236 billion in Europe and the U.S.A., respectively [4, 5]. Although antidepressants and psychotherapy (e.g. cognitive behavioral therapy, CBT) offer effective treatment options for MDD, a substantial group of patients does not respond adequately to treatment. Specifically, the percentage of patients that achieves remission after an antidepressant trial drops dramatically from approximately 35% for the first two trials to only 13% for a third or fourth trial, whereas the number of side effects and patients that stop treatment increases substantially [6]. Up to 35% of patients fail to respond to first line treatments and suffer from treatment-resistant depression (TRD) [6]. However, there is no unified definition of TRD (sometimes also referred to as difficult-to-treat-depression; DTD), which has been operationalized in various ways [7, 8]. For example, the Thase and Rush staging method defines five levels of treatment resistance, based on the number and classes of failed antidepressant treatment trials [9]. Alternately, Conway and colleagues propose a heuristic two stage-model of TRD with moderate and severe treatment resistance, largely based on the inflection point that is seen after two antidepressant treatment trials [10]. At this point, a different treatment modality with a different mechanism of action may be preferred over yet another antidepressant medication trial. In severe cases electroconvulsive therapy (ECT) would be such an option. However, despite its superior effectiveness, ECT is also invasive and comes with a risk of substantial side effects such as short term memory loss. Ideally, a less invasive treatment option would be available when antidepressants fail. Furthermore, irrespective of staging as a function of the number of failed treatments, longer periods of insufficient treatment lead to a higher risk of chronicity, comorbidity and suicidality, emphasizing the need for effective treatment options for patients with TRD [11].

Repetitive transcranial magnetic stimulation (rTMS) is a non-invasive neurostimulation method that is increasingly being used to treat MDD, with promising effects in TRD [12]. The therapeutic effect of rTMS is achieved by delivering magnetic pulses through a coil that is positioned above the head. The magnetic field induces an electrical current in the underlying cortex that modulates neuronal activity. Based on the observation of dysfunctional dorsolateral prefrontal cortex (DLPFC) activity in depressed patients in neuroimaging studies, the DLPFC was selected as the primary target for MDD [13, 14]. High-frequency stimulation over the left DLPFC or low-frequency stimulation over the right DLPFC can both be applied in order to modulate the brain circuits that are involved in depression [15]. In recent years a sufficient body of evidence has been build up to establish the definite antidepressant efficacy of high frequent rTMS over the left DLPFC and probable antidepressant efficacy of low frequent rTMS over the right DLPFC [16]. A recent meta-analysis that included 57 RCTs showed a significantly larger depressive symptom reduction after active rTMS compared to sham (Hedges’ g = − 0.832), and similar results were found for response and remission rate [17]. Evidence from a large naturalistic study (*n* = 196) in one of the participating centers indicates that combining rTMS with CBT even yields additional effects, contributing to robust remission rates of 56% in TRD [18]. This additive effect of combining rTMS with CBT has also been established in other psychiatric disorders, such as post-traumatic stress disorder and obsessive-compulsive disorder, as well as for combining antidepressant medication with CBT [19–22].

Despite being approved as a treatment for patients with TRD, the exact position of rTMS in the treatment algorithms of depression remains unclear. The biological steps within these algorithms usually follow a stepped-care approach, starting with multiple, subsequent psychopharmacological steps and ECT as the last step. Not much is known about the comparative efficacy of rTMS to other biological steps, although studies have compared rTMS to venlafaxine and ECT [23, 24]. Importantly, the efficacy of these biological treatments may also depend on the level of treatment resistance. It is therefore difficult for the treating physician to decide when rTMS should be considered as a treatment option for his or her patient. A few studies have performed economic evaluations, comparing rTMS to other antidepressant treatments. Results on the cost-effectiveness of rTMS compared to ECT show mixed results, with some studies suggesting rTMS and others ECT as the most cost-effective treatment [25–28], where the level of treatment resistance and severity of depression may be the crucial factor. When compared to antidepressant medication, rTMS resulted in slightly more quality of life at lower costs [29, 30]. However, no studies have assessed the cost-effectiveness of rTMS as a follow-up step in patients with moderate level of treatment resistance.

Therefore, we want to examine the comparative efficacy of rTMS combined with CBT as an alternative to the current next pharmacological steps (i.e., switch or augmentation of antidepressant) in a randomized controlled trial. We propose to investigate the effectiveness of rTMS in combination with CBT and continued antidepressant medication compared to the next step in the treatment algorithm, in a sample of patients with non-psychotic unipolar depression, who did not respond to two adequate antidepressant treatments. We aim at testing the effectiveness of both treatments in terms of clinical improvement and the prevention of recurrence over the course of 6 months, as well as the cost-effectiveness. Furthermore, we will examine effect decay or preservation up until 12 months. We also aim to explore the effects of the two treatments on specific symptoms associated with depression, such as anhedonia, anxiety, rumination, cognitive reactivity, and sleep. Finally, we aim to assess the effect of expectations regarding the treatment on its effectiveness.

## Methods

### Study design

In this pragmatic randomized controlled trial (RCT), patients are randomly assigned to one of two treatment conditions. In the first condition, treatment consists of rTMS combined with CBT and continued antidepressant medication, which will hereafter be referred to as the rTMS arm. In the second condition, treatment consists of a switch from the current antidepressant medication to a tricyclic antidepressant (TCA) or augmentation with lithium or a second-generation antipsychotic, also in combination with CBT. This will be referred to as the medication arm. The trial consists of 8 weeks of unblinded treatment followed by a follow-up of the cohort at four and 6 months from baseline onward. For a subgroup of the patients, an extended follow-up will take place at nine and 12 months from baseline onward to assess effect decay or preservation. See Fig. 1 for the CONSORT flowchart. Patients in the medication arm who did not recover to the medication intervention can receive rTMS after completion of the first 8 weeks of treatment.

**Fig. 1 Fig1:**
[figure not shown]
CONSORT flowchart

### Aims and hypotheses

Our primary objective is to quantify whether 8 weeks of treatment with rTMS will outperform medication in terms of improvement of depressive symptoms. We expect that rTMS is more effective than medication in reducing depressive symptoms in patients with TRD.

Our secondary objective is to perform a health evaluation consisting of a cost-effectiveness analysis (CEA) with treatment response and remission as outcomes and a cost-utility analysis (CUA) with quality adjusted life years (QALYs) gained as outcome. The CEA and CUA will be performed along-side the trial. We expect rTMS to be more cost-effective than medication.

Finally, we aim to perform exploratory analyses of the effect of rTMS on other symptoms associated with depression, compared to the effect of new medication on these symptoms. The symptoms consist of suicidality, anhedonia, anxiety, rumination, cognitive reactivity, and sleep. A second exploratory objective is to assess the effect of expectations regarding the treatment on its effectiveness.

### Participants

We aim to include 132 adult patients diagnosed with moderate to severe (HDRS > 16) unipolar MDD without psychotic symptoms, with failed response to at least two treatment trials with adequately dosed antidepressants and a current episode of less than 2 years. Exclusion criteria are: lifetime diagnosis of bipolar disorder, schizophrenia or schizoaffective disorder; current diagnosis of substance abuse disorder or organic brain syndrome; the presence of a concurrent significant medical condition impeding the ability to participate; previous treatment with rTMS or ECT; epilepsy, convulsion or seizure; serious head trauma or brain surgery; large or ferromagnetic metal parts in the head (except for a dental wire); implanted cardiac pacemaker or neurostimulator; or pregnancy. A subset of 92 patients will be part of the extended follow-up up to 12 months.

### Sample size calculation

The sample size calculation is based on the outcome of the rTMS arm in comparison to the medication arm. To flag up a clinically significant difference between rTMS and medication, we took an effect size of d = 0.33, which corresponds to the lower boundary of a medium clinically meaningful effect [31] and is similar to effect sizes for research on antidepressant medication [32]. Alpha will be set at 0.05, with a power (1-beta) of 0.80. We will employ a two-sided repeated measures ANCOVA, with a total of six repeated measurements (baseline and measurements corresponding to rTMS treatment 5, 10, 15, 20, and 25). See also Table 1 for an overview and timepoints of the measurements. Based on HDRS-17 data from one of our previous studies, we expect the correlation between baseline and follow-up to be *r* = 0.59, and the correlation between follow-up measurements to be *r* = 0.69. The sample size calculation was performed in STATA version 15.1 and resulted in an estimated required sample size of 59 participants per condition. Compensating for possibly 10% loss to follow-up, the total sample size at baseline will be increased to 132 participants.

**Table 1 Tab1:** Overview of rTMS sessions and measurements during the treatment period. For participants in the medication arm, measurements will be done on days corresponding to treatment day 5, 10, 15, 20, and 25 of rTMS treatment

	Week 1					Week 2					Week 3					Week 4				
Day	1	2	3	4	5	1	2	3	4	5	1	2	3	4	5	1	2	3	4	5
rTMS	x	x		x	x	x	x		x	x	x	x		x	x	x		x		x
HDRS						x						x								x
BDI-II						x						x								x
	Week 5					Week 6					Week 7					Week 8				
Day	1	2	3	4	5	1	2	3	4	5	1	2	3	4	5	1	2	3	4	5
rTMS	x		x		x	x		x		x		x		x			x		x	
HDRS								x											x	
BDI-II								x											x	

### Procedure

This is a multicenter trial, taking place within the Dutch specialized mental health care setting. Patients are recruited and treated at Radboud University Medical Center (Radboudumc; Nijmegen), Pro Persona mental health care (Nijmegen, Arnhem), neurocare (Nijmegen, Arnhem, Eindhoven, Den Haag), the Elisabeth TweeSteden Hospital (ETZ; Tilburg), GGZ inGeest mental health care (Amsterdam), the St. Antonius Hospital (Utrecht, Nieuwegein), and also recruited via the Dutch Depression Foundation. If patients are eligible for participation, the psychiatrists or psychologists approach them to participate in the trial, after which they are contacted by a researcher. Study information is provided and patients are contacted again after at least 24 h to discuss participation and discuss any remaining questions. If patients decide to participate, they are invited for a research intake, where they are asked to sign the informed consent form and all baseline measurements are conducted. Afterwards, patients are randomized by the principal investigator (see below).

At baseline and during treatment, questionnaires will be administered by the clinician or researcher. Patients also fill in questionnaires themselves, which are sent via email using the secure online data capture program for clinical trials, Castor EDC [33]. The questionnaires can be filled out via any personal device (e.g. computer, tablet, smartphone). The expected study duration is 39 months, and inclusion of patients started in August 2019.

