### Primary objective - depressive symptoms

Section A, B and D of the Structured Clinical Interview for DSM 5 disorders (SCID-I; 2018) will be used at baseline and after six and 12 months to assess depressive episodes and possible relapses/recurrences at follow up and extended follow-up. During intake, the SCID will also be used to assess presence of bipolar disorder or psychotic features. The SCID takes about 20 min to complete.

The Hamilton Depression Rating Scale 17 item version is an observer rated scale used to assess the severity of depressive symptoms (HDRS-17) [38]. The HDRS-17 is assessed during screening, treatment, follow-up and extended follow-up. Completion takes approximately 15 min. During the eight-week treatment period, the HDRS-17 will be administered every five rTMS treatments, and on corresponding days for participants in the medication arm. See Fig. 2 for the schedule during treatment. Response is defined as a ≥ 50% reduction in score on the HDRS-17, whereas remission is defined as a score of < 8. Response and remission will be determined after 8 weeks of treatment and at the final follow-up assessment of the RCT at 6 months after baseline.

The Beck Depression Inventory will be used in order to measure individual differences in depressive symptoms (BDI-II) [39]. Participants will be asked to fill in the BDI-II once every five rTMS sessions or on corresponding days when they are in the medication arm. See Fig. 2 for the schedule during treatment. Participants have to indicate on 21 items in how far these items describe themselves on a scale ranging from 0 to 3 resulting in a sum score between 0 and 63. The total score can further be divided into four ranges, describing the severity of depressive symptoms from minimal (0–13), mild (14-19), moderate (20-28) to serious depressive symptoms (29–63). Completion takes about 5 min.

Two questionnaires will be used to assess and quantify the level of treatment resistance. The Dutch Measure for quantification of Treatment Resistance in Depression (DM-TRD) quantifies treatment-resistant depression by assessing treatments in the depressive episode as well as functional impairment, comorbid anxiety, personality disorders and psychosocial stressors [40]. The DM-TRD generally takes 10-20 min to complete after the diagnostic interview. The Antidepressant Treatment History Form (ATHF) can be administered in 10 min or less, depending on the number of antidepressant trials of a patient [41].

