### Change in depression severity

Our primary outcome during the intervention is overall change in HDRS-17 depressive symptom severity during 8 weeks of treatment by condition (rTMS versus medication). Data will be collected at 6 timepoints: at baseline, and after 5, 10, 15, 20, and 25 rTMS treatment sessions (or corresponding days for participants in the medication arm). We will employ linear mixed modelling using marginal means, with HDRS-17 score as our dependent variable and treatment (rTMS or medication) as independent variable. Age and gender will be added as covariates, since these have been shown to affect the phenomenology of depression.

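### The protocol lets an arm-aware clinician score the observer-rated primary outcome (HDRS-17), does not require the rater to be independent of treatment, and does not acknowledge rater bias

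*Protocol article*

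**What the plan says.** All of this comes from the protocol article.

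- **Blinding.** Study design: "The trial consists of 8 weeks of unblinded treatment". No masked, independent or central assessor is mentioned anywhere.
- **Instrument.** Under the primary objective, the Hamilton scale "is an observer rated scale used to assess the severity of depressive symptoms (HDRS-17").
- **Primary outcome and model.** Change in depression severity: "Our primary outcome during the intervention is overall change in HDRS-17 depressive symptom severity during 8 weeks of treatment by condition". The linear mixed model is specified "with HDRS-17 score as our dependent variable and treatment (rTMS or medication) as independent variable".
- **Who rates.** Procedure: "At baseline and during treatment, questionnaires will be administered by the clinician or researcher". The next sentence deals separately with the forms that patients complete themselves online, so this one must cover the HDRS-17.
- **When.** During treatment "the HDRS-17 will be administered every five rTMS treatments, and on corresponding days for participants in the medication arm". The self-rated BDI-II follows the same timetable: "Participants will be asked to fill in the BDI-II once every five rTMS sessions or on corresponding days when they are in the medication arm". Table 1 marks both instruments on the same five days.
- **Other uses of the score.** Response and remission at 8 weeks are derived from the HDRS-17. Under Interventions, two consecutive scores below 8 are a condition for ending rTMS early.
- **Limitations.** Strengths and limitations covers treatment heterogeneity, non-specific effects and sham, selection, CBT format and follow-up length. It does not cover a rater's knowledge of the arm.

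**The concern.** Blinding patients and therapists is not practical in a pragmatic comparison of rTMS with medication. Who scores the outcome is a separate choice, and the article makes that choice in a way that leaves an avoidable opening for bias. The stated expectation is that rTMS will do better, the scale depends on an interviewer's judgement, and the rule allows that interviewer to be a clinician who knows the allocation.

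If raters score one arm systematically lower for the same clinical state, the difference adds directly to the treatment contrast. Adjusting for baseline does not remove it, because baseline is measured before randomisation and only the five later ratings are exposed. A larger sample does not remove it either: the standard error shrinks while the bias stays. The planned analysis of the HDRS-17 alone cannot separate such a shift from a treatment effect. The same scores feed response and remission at 8 weeks, so those would move with it. The targeted effect is modest (d = 0.33), so even a small shift would be a sizeable share of it.

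**Working it through.** **1. Reproduce the plan's own sample size.** Inputs from Sample size calculation: d = 0.33, two-sided alpha 0.05, power 0.80, one baseline and five later measurements, baseline-to-follow-up correlation 0.59, correlation between follow-ups 0.69, 59 per arm, 10% loss, 132 in total.

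Variance factor for the mean of five follow-ups adjusted for baseline, in units of the outcome variance:

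V = (1 + 4 × 0.69)/5 − 0.59² = 0.7520 − 0.3481 = 0.4039

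n per arm = 2 × V × (1.960 + 0.842)² / d² = 2 × 0.4039 × 7.849 / 0.1089 = 58.2, rounded up to 59.

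59/0.90 = 65.6, so 66 per arm and 132 in total. The stated figures reproduce.

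**2. Standard error of the contrast.** SE = √(2 × 0.4039/59) = 0.117 SD. A difference is significant once it exceeds 1.96 × 0.117 = 0.23 SD.

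**3. Effect of a rating shift.** Let b be a constant difference in scoring between arms, in SD units, with no true treatment effect. The chance of a significant result is

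Φ(b/SE − 1.96) + Φ(−b/SE − 1.96).

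No document gives b. The values below are assumed, to show a range.

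| Assumed b (SD) | b/SE at 59 per arm | Significant, 59 per arm | Significant, 66 per arm |
|---|---|---|---|
| 0 | 0 | 5% | 5% |
| 0.05 | 0.43 | 7.1% | 7.4% |
| 0.10 | 0.85 | 13.7% | 14.8% |
| 0.15 | 1.28 | 24.9% | 27.3% |
| 0.20 | 1.71 | 40.1% | 44.0% |

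A shift of 0.15 SD is 0.15/0.33 = 45% of the effect the trial is sized for. The last column shows that more patients make the problem slightly worse.

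**4. If only some ratings are affected.** Suppose half the ratings, again an assumption, are made by researchers who carry no such shift. The average shift then halves to 0.05, 0.075 or 0.10 SD, and the rates fall to about 7%, 10% and 14%. For the middle value, 0.075/0.117 = 0.64 and Φ(−1.32) + Φ(−2.60) is about 0.098.

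**5. Workload of the remedy.** At most 132 × 5 = 660 post-baseline ratings. At the article's 15 minutes each, that is 9,900 minutes, or 165 hours, over a study expected to last 39 months.

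**The case against.** The strongest reply is that the text says less than a critical reader may infer. Five inferences are tempting, and the article does not support them.

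- **That the person delivering rTMS rates the patient and decides when rTMS ends.** Procedure says clinician or researcher, without saying that the clinician is the treating one. The passage on ending rTMS names neither a rater nor a decision-maker. What stands is that the rule does not exclude someone involved in treatment.
- **That the two arms have different kinds of rater.** One rule is given for both arms. A difference is possible under it but is not stated.
- **That the bias carries through to cost per remitter.** That endpoint is remission at 6 months. The rater sentence covers only baseline and treatment, and the article does not say who rates later. Medication-arm patients who have not recovered can also receive rTMS after week 8, so a preference for rTMS would not simply favour one arm by then. Only the 8-week results follow from the text.
- **That the BDI-II has no role.** It is listed under the primary objective. The analysis sections name no BDI-II analysis, but a condensed article may leave that to the full protocol or SAP, so this is not a defect.
- **That superiority should depend on the BDI-II agreeing.** That would add a success criterion, and nothing in the documents calls for one.

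It is also fair to object that the size and direction of any bias are unknown, that the calculation assumes the same shift at every rating, and that 0.117 SD comes from the sample-size ANCOVA, whereas the analysis is a linear mixed model with age and gender as covariates. These points limit the figures to illustration. They do not touch the core: the rule as written permits arm-aware rating of a judgement-based primary outcome, and the limitations do not say so.

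**Conclusion.** The point holds as a cheap improvement, not as proof of bias. The article allows the only dependent variable of the primary model to be scored during open treatment by a clinician who knows the arm. It asks for neither independence nor masking and does not list this among its limitations. The exposure covers the primary contrast and response and remission at 8 weeks.

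The size is hypothetical. Under a constant between-arm shift of 0.10 to 0.20 SD, no true effect and the sample-size standard error, the false-positive rate rises from 5% to between about 14% and 40%. If half the ratings were unaffected, it would lie between about 7% and 14%. A shift in the other direction would hide a real benefit of rTMS. The sample size itself is correct and is unaffected.

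**What to change.** **Rater rule.** Amend Procedure so that, in both arms, every HDRS-17 rating after randomisation is done by the study researchers whom the article already names, and never by anyone who prescribes or delivers that patient's treatment. Where feasible, the rater should not be told the arm.

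**Patients already rated.** Inclusion began in August 2019. For ratings already made, record whether a clinician or a researcher did them, report this by arm, and add rater knowledge of the arm to the limitations.

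**Supportive analysis.** Fit the primary model to the BDI-II collected on the same days, with no success condition attached. State its limit: it removes rater bias but not the expectancy of patients who know their treatment, so it is a check on the HDRS-17 result and not a substitute for independent rating.

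**Cost.** At most about 165 hours of interviews are reallocated among existing roles, with some rescheduling. Patients will occasionally reveal their arm. The rating arrangement changes partway through recruitment, which is a further reason to report rater role by arm. Sample size and visits are unchanged, and the BDI-II analysis needs no new data.
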